### Procedure for unblinding if needed {17b}

Emergency unblinding will be permitted only when knowledge of the assigned intervention is essential for the clinical management of a serious adverse event.

## Data collection and management

### Plans for assessment and collection of outcomes {18a}

Each site will administer anesthesia, according to their institutional guidelines. Medication type, dosing, and additional analgesics administered, as per each site’s anesthesia protocol, will be documented, in detail, in the case report form (CRF). A qualified and experienced anesthesiologist will be required to complete the CRF.

Prior to study initiation, researchers will receive training on the study protocol, according to the principles of GCP for clinical trials.

### Plans to promote participant retention and complete follow-up {18b}

Data collection and outcome evaluation personnel will be conducted as in-person visits with participants from the preoperative day to 7 days postoperatively. Moreover, these personnel will follow up with participants or their guardians, telephonically, for 30 days postoperatively to gather data. The ARISCAT risk score will be used by the data collection and outcome evaluation personnel to evaluate the risk of PPCs.

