**Methods:**

This multicenter, prospective, parallel-cohort, randomized controlled clinical trial will include 1098 older adult participants aged ≥ 65 years old undergoing laparoscopic gastrointestinal surgery, from 16 clinical trial sites across China. Participants will be randomized, as per a 1:1 ratio to two cohorts, the “L” and “H” cohorts, to receive low FiO_2_ (40%) and high FiO_2_ (80%) levels, respectively. The primary outcome measure is the 48-h postoperative oxygenation index between the two cohorts. The secondary outcome measures include the other blood gas analysis results, PPCs within 7 days, and 30-day mortality rate.

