### Outcomes {12}

#### Primary outcome

The primary outcome measure is the comparison of the 48-h postoperative oxygenation index between the two cohorts. This will be derived from arterial blood gas sampling and analysis, in addition to the FiO_2_ 48th h postoperatively.

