For qualitative data of secondary outcomes—including postoperative PACU oxygenation rate, 24-h postoperative oxygenation rate, 48-h postoperative oxygenation rate, pulmonary complications at 7 days postoperatively, and 30-day mortality rate—generalized linear mixed-effects models were employed. The model included patient baseline data (age, gender, BMI, and history of SARS-CoV-2 infection), intraoperative characteristics (anesthesia duration, intraoperative crystalloid volume, intraoperative colloid volume, surgical duration, surgical position, pneumoperitoneum pressure, intraoperative PEEP, occurrence of pulmonary re-expansion, intraoperative ventilator tidal volume, and airway platform pressure), and center and group factors.

For ordinal outcomes such as postoperative PACU oxygen concentration, 24-h postoperative oxygen concentration, 48-h postoperative oxygen concentration, and severity of pulmonary complications, a generalized linear mixed-effects model was employed. The model included patient baseline data (age, gender, BMI, history of SARS-CoV-2 infection), intraoperative characteristics (anesthesia duration, intraoperative crystalloid volume, intraoperative colloid volume, surgical duration, surgical position, pneumoperitoneum pressure, intraoperative PEEP, occurrence of pulmonary re-expansion, intraoperative ventilator tidal volume, and airway platform pressure), and center and group factors.

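### The 7-day PPC and PPC-severity models leave out the ARISCAT risk score and adjust for ten intraoperative variables, some of which can respond to the allocated FiO2

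*Protocol article*

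**What the plan says.** Section {18b} introduces the score: "The ARISCAT risk score will be used by the data collection and outcome evaluation personnel to evaluate the risk of PPCs". It places these staff's visits between the preoperative day and day 7. It does not say when the score is calculated or whether it enters an analysis.

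The abstract ranks PPCs among the secondary outcomes: "The secondary outcome measures include the other blood gas analysis results, PPCs within 7 days, and 30-day mortality rate". Section {20a} then names the model for the binary outcomes: "pulmonary complications at 7 days postoperatively, and 30-day mortality rate—generalized linear mixed-effects models were employed". Its covariates come in two groups.

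- Baseline: "The model included patient baseline data (age, gender, BMI, and history of SARS-CoV-2 infection".
- Intraoperative: "intraoperative characteristics (anesthesia duration, intraoperative crystalloid volume, intraoperative colloid volume, surgical duration, surgical position, pneumoperitoneum pressure, intraoperative PEEP, occurrence of pulmonary re-expansion", and then "intraoperative ventilator tidal volume, and airway platform pressure), and center and group factors".

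The ordinal outcomes are handled alike ("severity of pulmonary complications, a generalized linear mixed-effects model was employed"), with the same covariates. ARISCAT appears in neither list, nor among the stratification factors in {16a}.

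**The concern.** Two things about these lists are unfavourable.

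First, they omit the one PPC-specific risk measure that the article names. In a logistic-type model, adjusting for a prognostic variable fixed before randomisation raises the power of the group comparison without biasing it. Section {14} sizes the trial on the oxygenation index and gives no power for PPCs, although it opens by describing the trial as one about PPCs. Power that costs little is therefore worth having here.

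Second, and more important, the lists include variables recorded after allocation. If the allocated FiO2 changes such a variable, conditioning on it removes the part of the effect that passes through it. It can also create an imbalance in other causes of PPCs that randomisation had balanced. The adjusted odds ratio then no longer estimates the total effect of the oxygen strategy, which is what the trial sets out to compare.

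**Working it through.** **1. The plan's own figure.** Section {14} gives pilot means of 384 and 340 mmHg (difference 44), a threshold of 30, SD 74, one-sided alpha 0.025 and power 80%. The distance to detect is 44 − 30 = 14.

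n per group = 2 × (1.960 + 0.842)² × 74² / 14² = 2 × 7.85 × 5476 / 196 ≈ 439

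439 / 0.80 = 548.75, rounded up to 549, and 2 × 549 = 1098. The stated figures reproduce, and this point leaves them unchanged. The evaluable number is 2 × 439 = 878.

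**2. Counting the covariates.** Baseline: age, gender, BMI, prior SARS-CoV-2 infection (4). Intraoperative: anesthesia duration, crystalloid, colloid, surgical duration, position, pneumoperitoneum pressure, PEEP, re-expansion, tidal volume, airway platform pressure (10). Center and group are added. ARISCAT is absent.

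**3. Can the intraoperative terms respond to allocation?**
- {16a} allocates on the preoperative day, so all ten realised values come later.
- {17a} leaves the anesthesiologists, who set the ventilator, unblinded.
- {11b} describes a response to falling saturation for the L cohort only, in which an airway-pressure step comes before the oxygen is raised. That can affect recorded PEEP, re-expansion and pressure in one arm.
- {6a} argues that high oxygen causes absorption atelectasis, which lowers lung compliance. Reading airway platform pressure as plateau pressure, static compliance = tidal volume / (plateau pressure − PEEP). All three terms are in the model, so it comes close to holding compliance fixed, which is part of the mechanism that the article proposes.

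**4. What the score could add.** The documents supply no PPC rate, PPC effect or prognostic strength, so every input here is an assumption.

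*Approximation.* If the score explains an extra fraction R² of outcome variance, effective sample size grows by 1/(1 − R²) − 1. The power column assumes PPC rates of 20% against 15% (risk ratio 0.75), 439 per group and one-sided 0.025.

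| Extra R² | Gain in effective n | PPC power |
|---|---|---|
| 0 | 0 | 49.6% |
| 0.02 | 2.0% | 50.4% |
| 0.05 | 5.3% | 51.6% |
| 0.10 | 11.1% | 53.8% |
| 0.15 | 17.6% | 56.2% |

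*Simulation.* The plan already adjusts for variables such as age and surgical duration, so the relevant gain is the increment over a model that holds a covariate correlated with the score. Settings: n = 878, odds ratio 0.65, PPC rate 20% or 30%, odds ratio per SD of score 1.5 to 2.7, correlation 0.3 or 0.5, 3000 trials per setting. Gains were about 0 to 5 points, for example 57.4% to 61.7% and 68.8% to 73.8% with a strong score. A repeat gave 0.3 to 5.5 points when the existing covariate was itself prognostic (log odds ratio 0.3 per SD). When that covariate had no effect of its own, the gain reached 6.8 points in the most favourable setting. With a weak score (1.5 per SD) every gain was under 2 points.

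*Where the gain comes from.* In one setting of the repeat (20% rate, 2.7 per SD, correlation 0.5, existing covariate without its own effect), adding the score moved the mean log odds ratio from −0.392 to −0.435 and its mean standard error from 0.184 to 0.194. The ratio rose from 2.13 to 2.24. The standard error grew; the estimate moved further from zero.

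**The case against.** The strongest reply is that choosing covariates for a secondary outcome is a matter of judgement. Section {18b} commits the score only to evaluating risk, and describing the population's risk is a complete use of it. Leaving it out does not invalidate the analysis. That stands: on its own, the omission costs only some power.

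The timing objection also stands. Visits start on the preoperative day, but randomisation falls on that day too, and the article does not list the score's components. A reader might infer that a pre-randomisation ARISCAT value already exists for everyone. The text does not say so.

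On size, comparing the score with an unadjusted model shows gains of up to 8 points in the most favourable assumed case. A reader might take that as the loss. It is the wrong comparison, because the planned models already contain other predictors. Nor has the full swap been simulated: dropping prognostic terms such as surgical duration could offset the gain.

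Finally, {11a} sets common ranges for PEEP and tidal volume in both arms, which limits how far they can diverge. This weakens the case for those two terms. It does not reach re-expansion or airway platform pressure, nor the response in {11b} that applies to one arm. The judgement defence also fails for the post-randomisation terms, because {20a} lists them explicitly and names no PPC model without them.

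**Conclusion.** The point holds as a modest improvement to two secondary-outcome models. The article names a PPC risk score and omits it from the PPC models, while including ten variables measured after randomisation, some of which can carry or distort the effect of FiO2.

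The second half matters more, but its size cannot be computed: the documents give nothing on how far the intraoperative variables differ by arm, so distortion is possible and not demonstrated. The first half is worth about 0 to 5 points of power under the stated assumptions, and close to nothing if the score is weak.

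Three stronger readings are tempting and unsupported:
- The intraoperative variables do not replace baseline adjustment. Four baseline variables and center are in the models.
- PPCs are not the trial's main outcome in its own terms. They motivate it, but section {12} is explicit: "The primary outcome measure is the comparison of the 48-h postoperative oxygenation index between the two cohorts".
- What is forgone is power. The standard error of the conditional odds ratio does not shrink on adjustment, so it is inaccurate to call the loss one of precision.

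**What to change.** In {20a}, define the main models for 7-day PPCs and PPC severity with age, gender, BMI, prior SARS-CoV-2 infection, ARISCAT, center and group. Move any model containing the intraoperative variables to a sensitivity analysis, labelled as conditional on post-randomisation values. If surgical position or operative time is truly used to stratify under {16a}, the planned value recorded at allocation counts as a pre-randomisation variable and may stay; the realised value should not.

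In {18b}, state that ARISCAT is calculated for every participant from values known before randomisation.

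The cost is mainly wording, settled before unblinded outcome data are seen. Two small burdens remain. Sites must be able to supply the score's inputs as they stood before allocation; if some were not recorded then, they have to be retrieved from preoperative records. And prognostic intraoperative terms such as surgical duration leave the main model, which may give back some of the power gained. Sample size, consent and treatment are unaffected.

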### Data management {19}

The data will be managed and analyzed according to the GCP guidelines and handled with strict confidentiality. Trained professionals will enter all trial data into an electronic CRF (eCRF). The eCRF should be completed promptly after data collection, and any missing data should be appropriately explained. A copy of the clinical trial sites’ data will be retained. A data inspector will verify the accuracy and completeness thereof, before sending the eCRF to the trial scheduling center.

Clinical quality inspectors will monitor the data at each center, and the data will be checked by means of electronic CRFS at a frequency of every 30 cases.

### Confidentiality {27}

The collected data will be processed anonymously and stored securely for the exclusive purposes of the researchers and supervisors. Data will be maintained for up to 5 years to support the research project and subsequently archived in an anonymous format.

The data generated during the trial, at the First Hospital of China Medical University, will be provided at no cost, and the digital object identifier systems for these data will be made available, once articles utilizing the data are published. Issues pertaining to security, licensing, or ethical requirements regarding the intended data are not expected. Any data associated with a previously published article will be included with the current article on publication.

### Plans for collection, laboratory evaluation, and storage of biological specimens for genetic or molecular analysis in this trial/future use {33}

N/A. Our trial does not involve biological specimens for genetic or molecular analysis.

## Statistical methods

### Statistical methods for primary and secondary outcomes {20a}

The oxygenation index data for the two cohorts will be collected, based on a preliminary experiment. The oxygenation index values will be presented as means and standard deviations.

The Student’s *t*-test will be used to assess the disparities between the two cohorts for continuous outcome variables adhering to a normal distribution. In cases of non-normal distribution, the Mann–Whitney test will be used. Categorical data will be analyzed, using the chi-squared or Fisher’s exact tests. These tests are one-sided, and statistical significance will be set at *p* < 0.025. The parameters will be computed and displayed, including approximations and a 97.5% confidence interval.

The primary and secondary outcome indicators will be evaluated using linear and generalized linear mixed-effects models.

A linear mixed-effects model was employed to analyze the primary outcome measures (oxygenation index and quantitative variables). The model included patient baseline data (age, gender, BMI, and prior SARS-CoV-2 infection history), intraoperative characteristics (anesthesia duration, intraoperative crystalloid volume, intraoperative colloid volume, surgical duration, surgical position, pneumoperitoneum pressure, intraoperative PEEP, occurrence of pulmonary re-expansion, intraoperative ventilator tidal volume, and airway platform pressure), and center and group factors.

For quantitative secondary outcome measures—including postoperative PACU oxygen duration, 24-h and 48-h oxygen therapy duration, and postoperative blood gas parameters (pH, partial pressure of carbon dioxide, and lactate) at 48 h—linear mixed-effects models were employed. The model included patient baseline characteristics (age, gender, BMI, and prior SARS-CoV-2 infection history) and intraoperative parameters (anesthesia duration, intraoperative crystalloid volume, colloid volume, surgical duration, surgical position, pneumoperitoneum pressure, intraoperative PEEP, occurrence of pulmonary re-expansion, and ventilator tidal volume), along with center and group factors.

For qualitative data of secondary outcomes—including postoperative PACU oxygenation rate, 24-h postoperative oxygenation rate, 48-h postoperative oxygenation rate, pulmonary complications at 7 days postoperatively, and 30-day mortality rate—generalized linear mixed-effects models were employed. The model included patient baseline data (age, gender, BMI, and history of SARS-CoV-2 infection), intraoperative characteristics (anesthesia duration, intraoperative crystalloid volume, intraoperative colloid volume, surgical duration, surgical position, pneumoperitoneum pressure, intraoperative PEEP, occurrence of pulmonary re-expansion, intraoperative ventilator tidal volume, and airway platform pressure), and center and group factors.

For ordinal outcomes such as postoperative PACU oxygen concentration, 24-h postoperative oxygen concentration, 48-h postoperative oxygen concentration, and severity of pulmonary complications, a generalized linear mixed-effects model was employed. The model included patient baseline data (age, gender, BMI, history of SARS-CoV-2 infection), intraoperative characteristics (anesthesia duration, intraoperative crystalloid volume, intraoperative colloid volume, surgical duration, surgical position, pneumoperitoneum pressure, intraoperative PEEP, occurrence of pulmonary re-expansion, intraoperative ventilator tidal volume, and airway platform pressure), and center and group factors.

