## Assignment of interventions: allocation

### Sequence generation {16a}

Post-initiation of the study, each clinical trial site will continuously screen eligible participants and enroll them in the trial. Participants will be randomly assigned. The study employed block randomization with center stratification, where each center competed for inclusion. The electronic data capture (EDC) system generated the randomization. The participants will be assigned to two cohorts, as per a 1:1 ratio, on the preoperative day. To balance the variables, we will stratify the participants according to the following factors: age, surgical position, area of the clinical trial site, operative time, and the anesthetic drug administration and method.

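### The tests that carry the 0.025 threshold ignore the randomisation strata, the plan does not say whether they or the mixed models decide the primary outcome, and the models omit one stated stratum (anaesthetic drug and method)

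*Protocol article*

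**What the plan says.** Protocol article, Sequence generation {16a}: "The study employed block randomization with center stratification, where each center competed for inclusion". Allocation takes place before surgery: "The participants will be assigned to two cohorts, as per a 1:1 ratio, on the preoperative day". The section then says that participants will also be stratified by "age, surgical position, area of the clinical trial site, operative time, and the anesthetic drug administration and method".

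Protocol article, Statistical methods for primary and secondary outcomes {20a}, gives two sets of analyses.

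- **Plain two-sample tests.** Student's t-test "will be used to assess the disparities between the two cohorts for continuous outcome variables adhering to a normal distribution", with Mann-Whitney for non-normal data. For the rest: "Categorical data will be analyzed, using the chi-squared or Fisher’s exact tests". The one-sided threshold of p < 0.025 is attached to these tests. No stratum is named for any of them.
- **Mixed models.** "The primary and secondary outcome indicators will be evaluated using linear and generalized linear mixed-effects models". Four covariate lists follow: for the primary outcome, and for quantitative, qualitative and ordinal secondary outcomes. Each contains age, surgical position, surgical duration, centre and group. The primary list, for example, ends with "intraoperative ventilator tidal volume, and airway platform pressure), and center and group factors". None of the four contains anaesthetic drug or method. No significance threshold is attached to the models.

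**The concern.** When allocation is blocked within strata, the arms are balanced on those factors by design, and variation between strata largely drops out of the treatment contrast. A test that ignores the strata still counts that variation as error. Its reported standard error is then larger than the true one, its interval is too wide, and its real one-sided error falls below the nominal 2.5%.

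Two features of the text raise the question. First, the only analyses given a decision threshold are the unstratified ones, while adjusted models are planned for the same outcomes with no ranking between the two. Second, the models carry long covariate lists, down to fluid volumes and pneumoperitoneum pressure, yet omit one factor that the randomisation section names. That factor does vary between patients: Intervention description {11a} allows combined, total intravenous or inhalation anaesthesia.

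At stake are some precision on the primary outcome and a choice between an unadjusted and an adjusted result that the text leaves open.

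**Working it through.** **1. Reproduce the plan's sample size.** Inputs from Sample size {14}: pilot means 384 and 340 mmHg, threshold 30 mmHg, SD 74, one-sided α = 0.025, β = 0.20, dropout 20%.

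- Net effect: 384 − 340 − 30 = 14 mmHg.
- n per group = 2 × 74² × (1.960 + 0.842)² / 14² = 439 after rounding up.
- With dropout: 439 / 0.80 = 548.75, so 549 per group and 2 × 549 = 1098 in total.

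Both stated figures match. A difference of 30 gives 96 per group and a difference of 44 gives 45, so the plan was sized on a net 14 mmHg. The SD is the total, unadjusted one: √((85² + 60²)/2) = 73.6, rounded up to 74.

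**2. Compare the strata with the analyses.**

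| Stated stratum | Plain tests | All four models |
|---|---|---|
| Centre | no | yes |
| Age | no | yes |
| Surgical position | no | yes |
| Area of site | no | through centre |
| Operative time | no | yes, as surgical duration |
| Anaesthetic drug and method | no | **no** |

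**3. Size if the plain t-test decides.** Let R² be the share of oxygenation-index variance that the strata explain. The documents do not give it, so it is assumed.

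- Reported standard error: s0 = 74 × √(2/439) = 4.995.
- True standard error under stratified allocation: s1 = s0 × √(1 − R²).
- Excess interval width: s0/s1 − 1.
- True one-sided error: 1 − Φ(1.960 × s0/s1).
- Power of the plain test: Φ((14 − 1.960 × s0)/s1).
- Power with strata: Φ(14/s1 − 1.960).

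| Assumed R² | Interval too wide by | True one-sided error | Power, plain test | Power with strata |
|---|---|---|---|---|
| 0 | 0% | 2.5% | 80.0% | 80.0% |
| 0.02 | 1.0% | 2.4% | 80.3% | 80.8% |
| 0.05 | 2.6% | 2.2% | 80.6% | 82.0% |
| 0.10 | 5.4% | 1.9% | 81.3% | 84.0% |
| 0.20 | 11.8% | 1.4% | 82.7% | 88.0% |

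The plain test never falls below the planned 80%. The gain forgone is 0.5, 1.4, 2.7 and 5.3 points in the last four rows.

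**4. Size if the mixed model decides.** Only the anaesthetic factor is missing. Using the same formulas, and the same total SD as an approximation:

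- R² = 0.01: interval 0.5% too wide; power 80.2% against 80.4%, about 0.3 points.
- R² = 0.05: interval 2.6% too wide; power 80.6% against 82.0%, about 1.4 points.

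**5. Check by simulation.** Set-up: 16 centres, one binary anaesthetic factor, blocks of 4, n = 878, 4000 runs, with centre assumed to explain 10% and the anaesthetic factor 5% of variance. Power was 81% for the t-test, 84% with centre only and 85% with both. One-sided error was 0.020, 0.025 and 0.028, with a Monte Carlo standard error of about 0.0025. This agrees with the formulas.

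**The case against.** The strongest reply is that the plan already does most of what is asked. Mixed models are announced for the primary and secondary outcomes, and every one holds centre, age, surgical position and surgical duration, with area of site covered through centre. If they decide, one factor is missing and the loss is very small.

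That factor may also not be a real stratum. The randomisation section first describes centre-stratified blocks and only then lists further factors. One of these, operative time, cannot be known on the day before surgery, when allocation is made. If the EDC system used centre alone, the models already match the randomisation and the list in {16a} is what needs correcting. Sites also give anaesthesia by their own institutional guidelines (Plans for assessment and collection of outcomes {18a}), so centre may absorb part of the anaesthetic factor.

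All of this stands, and it limits the size of the point. It does not remove it. The article itself attaches the threshold to the unstratified tests, lists the randomisation factors and sets out four covariate lists in full, and these do not agree with one another.

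The normal-theory figures also have a limit that must be granted: they apply to the continuous outcome only. For the binary models the link is not stated. With a logit link, omitting a prognostic covariate pulls the odds ratio towards one and does not widen its standard error.

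**Conclusion.** The mismatch between the randomisation and the analysis is real, and its consequence is modest: conservatism if the plain t-test decides, and very little if the mixed model does. The size depends on an assumed share of variance explained by the strata. The power figures also assume a test against the 30 mmHg margin, which the sample size implies but {20a} does not state.

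A reader might infer three stronger things, none of which the document supports.

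- **That power is lost against the plan.** It is not. The 439 per group was computed from the unadjusted SD, so an unadjusted comparison keeps at least 80%.
- **That the false-positive rate is inflated.** The shift goes the other way, to below 2.5%.
- **That the intervals are certainly too wide, in every test and model.** This holds only if the strata predict the outcome, which the document does not quantify, and the argument does not carry over to the binary models.

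Severity: minor. It is worth correcting because the correction is nearly free. It brings the test back to its nominal error, can improve precision on the primary outcome, and settles beforehand which result counts.

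**What to change.** 1. Reconcile {16a} with {20a}: state the factors that the EDC system actually stratified by.
2. Name one deciding analysis for the primary outcome: a linear model with group, centre and those strata, using the stratum values entered at randomisation. Attach the one-sided 0.025 threshold to it.
3. For binary outcomes, use a centre-stratified (Cochran-Mantel-Haenszel) test or the planned model, and say which.
4. Keep the plain t, Mann-Whitney, chi-squared and Fisher tests as descriptive.
5. Add anaesthetic method to the four covariate lists only if it was truly a randomisation stratum. If not, remove it from the list in {16a} and leave the models without it.

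The cost is wording in two sections and a check of the EDC configuration. No patients, visits or measurements are added. This assumes that the stratum values are held in the EDC system; the article says that the system generated the randomisation but does not say this outright.

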### Objectives {7}

#### Primary objective

To investigate whether varying levels of intraoperative FiO_2_ affect the 48-h postoperative oxygenation index in older adult participants who have undergone laparoscopic gastrointestinal surgery.

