### Sample size {14}

This randomized controlled trial aimed to examine the effect of varying intraoperative oxygen concentrations on PPCs. This study is a superiority trial in which the optimal effect threshold has been set. Based on a preliminary experiment, 10 samples were collected each group, and the values of oxygenation index were expressed as mean ± standard deviation: 384 ± 85 mmHg for 40% group and 340 ± 60 mmHg for 80% group. This study was designed as a superiority trial, with a clinically significant difference defined as an increase in oxygenation index by at least 30 (10% of 300 acute lung injure oxygenation index) in favor of 40% group compared to 80% group. The pooled standard deviation was estimated to be 74 mmHg. The sample size required for each group to achieve a significant difference, with a one-sided *α* = 0.025 and *β* = 0.20. The minimum sample size required for each group was approximately 439, with a total of 1098 samples needed for both groups, considering a dropout rate of 20%.

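### One-sided 0.025 testing is extended to secondary outcomes that have no stated test direction, does not fit an ordinary chi-squared test, and comes with a 97.5% interval whose sidedness is not given

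*Protocol article*

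**What the plan says.** Section 20a of the protocol article covers primary and secondary outcomes. It assigns the t-test to "assess the disparities between the two cohorts for continuous outcome variables adhering to a normal distribution", with Mann-Whitney where normality fails. For the rest, "Categorical data will be analyzed, using the chi-squared or Fisher’s exact tests". It then states "These tests are one-sided, and statistical significance will be set at" p < 0.025, and continues: "The parameters will be computed and displayed, including approximations and a 97.5% confidence interval". Whether that interval is one- or two-sided is not said.

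The same section next says that primary and secondary outcomes will be evaluated with linear and generalized linear mixed models. Seven-day pulmonary complications and 30-day mortality are among the outcomes named there. The sidedness of the group effect in these models is not given.

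The sample size section (14) is the only place that fixes a direction for a test. It plans superiority, defined as "an increase in oxygenation index by at least 30 (10% of 300 acute lung injure oxygenation index) in favor of 40% group", and uses "The sample size required for each group to achieve a significant difference, with a one-sided" alpha of 0.025. The primary objective itself has no direction: "To investigate whether varying levels of intraoperative FiO_2_ affect the 48-h postoperative oxygenation index". The Background and Discussion ask whether low FiO2 reduces pulmonary complications, but no test direction is set for them. None is set for pH, PaCO2, lactate, oxygen use or mortality either.

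**The concern.** A one-sided test is defined only once its direction is fixed. For the primary outcome the sample size section does that. For the secondary outcomes an analyst has two options, and both are poor:

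- Choose the direction after seeing the data. The nominal 2.5% error rate is then really 5%.
- Carry over the direction favouring 40%. An excess of complications or deaths with 40% FiO2 then gives a p-value near 1 and is reported as not significant, although the introduction cites evidence on both sides and calls the question controversial.

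The chi-squared test adds a further problem. Its usual statistic squares the difference and so ignores direction. Two analysts following section 20a could use different critical values and disagree about the same table.

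The unlabelled 97.5% interval leaves open whether the test and the interval for the primary outcome must agree.

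**Working it through.** **Inputs.** From the sample size section: pilot means 384 and 340 mmHg (difference 44), margin 30, SD 74, one-sided alpha 0.025, power 0.80, 439 per group, 20% dropout, 1098 in total. Pulmonary complication rates are not given, so those used below are assumptions.

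**1. The plan's own figure.** n per group = 2 × SD² × (z_alpha + z_beta)² / (difference − margin)² = 2 × 74² × (1.960 + 0.842)² / 14² = 438.6, so 439. Dropout: 439 / 0.80 = 548.75, so 549 per group and 1098 in total. The plan's figures reproduce. A two-sided alpha of 0.05 uses the same critical value, 1.960, and gives the same 439.

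**2. The interval.** SE = 74 × √(2/439) = 4.99 mmHg.

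| Reading of the 97.5% interval | Critical value | Distance needed beyond the null | Power, primary margin test |
|---|---|---|---|
| One-sided bound (same as two-sided 95%) | 1.960 | 9.79 mmHg | Φ(14/4.99 − 1.960) = 80.0% |
| Two-sided | 2.241 | 11.20 mmHg | Φ(14/4.99 − 2.241) = 71.3% |

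The width ratio is 2.241 / 1.960 = 1.14. On the two-sided reading, a result with one-sided p between 0.0125 and 0.025 passes the test but not the interval. Restoring 80% power would take 532 per group, or 665 with dropout (1330 in total).

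**3. Chi-squared.** On one degree of freedom, p < 0.025 needs a statistic above 2.241² = 5.02. A directional test at 0.025 corresponds to 1.960² = 3.84. Results between these values are significant in the favoured direction by one reading and not by the other.

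For example, assume complication rates of 14% with 40% FiO2 and 19% with 80%. The pooled SE is √(0.165 × 0.835 × 2/n), and the statistic is 4.98 with 549 per group and 3.98 with 439. Both lie in the gap.

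**4. An excess with 40% FiO2.** Assume 20% with 40% FiO2 and 14% with 80%, so the pooled rate is 17%, and take n with and without the planned dropout.

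| n per group | z = 0.06 / √(0.17 × 0.83 × 2/n) | Two-sided p | One-sided p, direction favouring 40% |
|---|---|---|---|
| 549 | 2.65 | 0.008 | 0.996 |
| 439 | 2.37 | 0.018 | 0.991 |

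The directional test cannot report this excess. The ordinary chi-squared test judged at 0.025 would report it, since 0.008 and 0.018 are both below 0.025. Its power for these rates with 549 per group is 65.8%, against 75.4% at two-sided 0.05.

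**5. Direction chosen afterwards.** 2 × 0.025 = 0.05.

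**The case against.** The strongest reply is that the text says less than a reader might infer. Four stronger readings are tempting, and the protocol does not support them.

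- **Harm from 40% can never be declared.** This holds only if the secondary tests take the direction favouring 40%. If the ordinary chi-squared p-value is compared with 0.025, the excess in step 4 is declared. A two-sided 97.5% interval would also show it: 6 ± 2.241 × 2.26 percentage points, about 0.9 to 11.1 with 549 per group. The directional reading and the chi-squared reading are alternatives and cannot be combined.
- **The interval contradicts the primary test.** It does so only if two-sided. The interval is mentioned directly after the one-sided 0.025 rule, so a one-sided 97.5% bound is a fair reading, and it agrees with the test exactly.
- **Every analysis is one-sided.** The rule covers four named tests. The mixed models are given no sidedness, and the protocol does not show that the unadjusted tests decide the conclusions on complications or mortality.
- **Safety outcomes are covered.** They are mentioned only under the handling of nonadherence and missing data (20c), where no test is named.

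The non-directional primary objective is also no case against the primary test, because the sample size section supplies the direction.

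All of this narrows the point. It does not remove it: section 20a still applies one-sided testing to outcomes with no set direction and to a test that has none, and still leaves the interval unlabelled. These are stated rules, not details left to a separate analysis plan.

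**Conclusion.** The point holds in limited form. One-sided 0.025 is acceptable for the primary superiority test. For the secondary outcomes under the four listed tests, the rule is either undefined, with a true 5% error rate if the direction follows the data, or blind to an excess with 40% FiO2 if it follows the primary. For 2x2 tables analysed by ordinary chi-squared it is stricter than a directional 0.025 test (5.02 against 3.84).

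The fall from 80% to 71% power and the 14% extra width arise only if the 97.5% interval is two-sided and decides the primary margin test. The complication rates are assumptions chosen for illustration; the critical values do not depend on them. The defect is one of wording, but it affects how results on complications and mortality could be reported.

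**What to change.** In section 20a:

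1. Confine one-sided 0.025 to the primary superiority-margin test, and state there that the direction is 40% over 80%.
2. Test all secondary outcomes two-sided at 0.05, and say that this also applies to the group effect in the mixed models.
3. Replace the 97.5% interval with a two-sided 95% confidence interval throughout. Its lower limit uses the same critical value, 1.960, as the one-sided 0.025 primary test, so the two will agree.

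The cost is wording only; the sample size remains 439 per group and 1098 in total. A secondary benefit in a pre-stated direction would be judged two-sided, but at 0.05 that has the same critical value as one-sided 0.025, so no power to show it is lost.
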